# The protocol of a prospective, multicenter, randomized, controlled phase III study evaluating different cycles of oxaliplatin combined with S-1 (SOX) as neoadjuvant chemotherapy for patients with locally advanced gastric cancer: RESONANCE-II trial

**DOI:** 10.1186/s12885-020-07764-7

**Published:** 2021-01-05

**Keywords:** Locally advanced gastric cancer, Duration of neoadjuvant chemotherapy, S-1, Oxaliplatin

## Abstract

**Background:**

Curing locally advanced gastric cancer through surgery alone is difficult. Adjuvant and neoadjuvant chemotherapy bring potential benefits to more patients with gastric cancer based on several clinical trials. According to phase II studies and guidelines, SOX regimen as neoadjuvant chemotherapy is efficient. However, the optimal duration of neoadjuvant chemotherapy has not been established. In this study, we will evaluate the efficacy and safety of different cycles of SOX as neoadjuvant chemotherapy for patients with locally advanced gastric cancer.

**Methods:**

RESONANCE-II trial is a prospective, multicenter, randomized, controlled phase III study which will enroll 524 patients in total. Eligible patients will be registered, pre-enrolled and receive three cycles of SOX, after which tumor response evaluations will be carried out. Those who show stable disease or progressive disease will be excluded. Patients showing complete response or partial response will be enrolled and assigned into either group A for another three cycles of SOX (six cycles in total) followed by D2 surgery; or group B for D2 surgery (three cycles in total). The primary endpoint is the rate of pathological complete response and the secondary endpoints are R0 resection rate, three-year disease-free survival, five-year overall survival, and safety.

**Discussion:**

This study is the first phase III randomized trial to compare the cycles of neoadjuvant chemotherapy using SOX for resectable locally advanced cancer. Based on a total of six to eight cycles of perioperative chemotherapy usually applied in locally advanced gastric cancer, patients in group A can be considered to have completed all perioperative chemotherapy, the results of which may suggest the feasibility of using chemotherapy only before surgery in gastric cancer.

**Trial registration:**

Registered prospectively in the World Health Organization International Clinical Trials Registry Platform (WHO ICTRP) with registration number ChiCTR1900023293 on May 21st, 2019.

## Background

Gastric cancer remains the third leading cause of malignant tumor death both in China and worldwide [1, 2]. The overall five-year survival rate is about 20% [3]. At present radical gastrectomy is regarded as the only approach to curing gastric cancer. However, about 30% of patients with gastric cancer have recurrence after receiving radical gastrectomy [4, 5]. Thus it is difficult to achieve a cure for gastric cancer through surgery alone.

Several randomized controlled trials have evaluated the efficacy of adjuvant chemotherapy, that is, postoperative chemotherapy, for gastric cancer recently. The ACTS-GC phase III trial enrolled 1059 patients with stage II or III gastric cancer at 109 centers throughout Japan. They were assigned randomly to either the S-1 group for receiving S-1 as adjuvant chemotherapy for 1 year postoperatively or the surgery-only group for receiving surgery alone. The five-year overall survival rates in the S-1 group and surgery-only group were 71.7 and 61.1% respectively, and the five-year relapse-free survival rates were 65.4 and 53.1% respectively. S-1 reduced the risk of death by 33.1% and of relapse by 34.7% [6]. The CLASSIC trial enrolled 1035 patients at 35 cancer centers in South Korea, China Mainland and Taiwan. Patients with stage II-IIIB gastric cancer who underwent D2 radical gastrectomy were assigned randomly to adjuvant chemotherapy with eight cycles of capecitabine and oxaliplatin (XELOX) or observation alone. The results showed that 27% of patients in the adjuvant capecitabine and oxaliplatin group and 39% in the observation alone group had recurrence or died (*P*< 0.0001) and the estimated five-year disease-free survival rates were 68 and 53% respectively [7]. These two trials from Asia confirmed that adjuvant chemotherapy using S-1 or XELOX could improve survival in patients with gastric cancer who had received D2 gastrectomy.

Unlike in Asia, in western countries, neoadjuvant chemotherapy, that is, perioperative chemotherapy, received widespread interest. The MAGIC trial was the first study to confirm the efficacy of neoadjuvant chemotherapy in gastric cancer treatment. A total of 503 patients with resectable adenocarcinoma of the stomach, esophagogastric junction or lower esophagus were enrolled and then assigned to either the perioperative-chemotherapy group or surgery group. Three cycles of preoperative and three cycles of postoperative chemotherapy using epirubicin, cisplatin and fluorouracil (ECF) were administrated to patients only in the perioperative-chemotherapy group, which resulted in a higher five-year survival rate than that of the surgery group (36% vs 23%, *P*=0.009) [8]. Afterwards, the FNCLCC/FFCD 9703 phase III trial was conducted in France to investigate the benefit of perioperative fluorouracil plus cisplatin (CF) in resectable gastroesophageal adenocarcinoma. Two hundred twenty-four patients were randomly assigned to either the perioperative chemotherapy and surgery group (CS group) medicated with two or three cycles of CF before surgery and three or four cycles after surgery, or the surgery alone group (S group) for receiving surgery only. The results showed that the CS group had a better five-year overall survival (38% vs 24%, *P*=0.02) and five-year disease-free survival (34% vs 19%, *P*=0.003) and that the perioperative chemotherapy significantly improved the curative resection rate (84% vs 73%, *P*=0.04) [9]. However, the completion rate of perioperative chemotherapy in these two trials was relatively low. Later, the FLOT4 trial altered the situation. It aimed to compare the safety and efficacy of FLOT (fluorouracil plus leucovorin, oxaliplatin and docetaxel) with that of ECF/ECX (epirubicin, cisplatin and fluorouracil or capecitabine). Seven hundred sixteen patients were enrolled and randomly assigned to treatment in 38 German hospitals. Results showed that the median overall survival and chemotherapy completion rate were increased in the FLOT group (50 months vs 35 months, *P*=0.012; 46% vs 37%), which indicated that FLOT could be preferred compared to ECF/ECX [10].

Although all trials mentioned above had positive findings, the EORTC 40954 study, which was conducted in Europe, showed no survival benefit for neoadjuvant chemotherapy. This trial was for the purpose of proving the superiority of preoperative chemotherapy using cisplatin, d-L-folinic acid and fluorouracil. Compared with the surgery-only group, the neoadjuvant group had higher R0 resection rate (81.9% vs 66.7%, *P*=0.036) and less lymph node metastases (61.4% vs 76.5%, *P*=0.018). Survival benefit was not demonstrated after median follow-up of 4.4 years and 67 deaths (HR 0.84, 95% Cl 0.52 to 1.35, *P*=0.466). Notably, because of the poor accrual, the trial was terminated and only 144 patients were randomly assigned in the neoadjuvant arm or surgery-alone arm (72:72) instead of an estimated total of 360 patients. The low statistical power, the high rate of proximal gastric cancer and the better outcome than expected due to the high quality of surgery were possible reasons for no survival benefit [11].

Recently, S-1 plus oxaliplatin (SOX) as neoadjuvant chemotherapy showed relatively high efficacy and safety in several studies [12–14]. A phase II trial conducted by our medical center demonstrated that neoadjuvant chemotherapy with SOX regimen yielded an overall response rate of 68.8% and a disease control rate of 93.8%. The D2 lymph nodes dissection rate and R0 resection rate in neoadjuvant chemotherapy group were both higher than those in surgery-only group [15]. Furthermore, fluoropyrimidine plus oxaliplatin was recommended in the National Comprehensive Cancer Network (NCCN) Guidelines Version 1.2020 Gastric Cancer and the Chinese Society of Clinical Oncology (CSCO) guidelines for the diagnosis and treatment of gastric cancer (2019) [16, 17]. Therefore, the SOX is considered to have good application prospects.

It should be noted that the number of cycles of preoperative chemotherapy applied in these studies is not standardized and two to four cycles seemed to be acceptable based on previous studies [8–10]. So, the proper duration for neoadjuvant therapy needs to be settled. A randomized phase II trial conducted in Japan enrolled 83 patients with stage III and IV resectable gastric cancer. They were randomly assigned into two courses of SC (S-1 plus cisplatin), four courses of SC, two courses of PC (paclitaxel plus cisplatin) and four courses of PC. The study found no significant differences between two regimens (*P*=0.956) or between the two- and four- course treatments (*P*=0.723). However, the limitations of the study are the relatively small sample size and the inclusion of some stage IV patients, which could lead to the negative result [18].

Based on these findings, the randomized phase III RESONANCE-II trial was designed to evaluate the efficacy and safety of different cycles of SOX as neoadjuvant chemotherapy for patients with locally advanced gastric cancer, so as to provide a theoretical basis for setting an optimal duration of neoadjuvant chemotherapy.

## Methods

RESONANCE-II trial is a prospective, multicenter, randomized, controlled phase III study which will be conducted in 29 medical centers in China and one medical center in Korea. Chinese PLA General Hospital is the lead center. [name] is the trial principal investigator (PI). All screened patients should state that they are healthy and have no discomfort, then they will sign the informed consent. After signing the informed consent, they will receive consultation from investigator and examinations. Eligible patients will be registered, pre-enrolled. Main possible reasons for screening failure include: (1) The results of physical examination or laboratory tests do not meet the inclusion criteria or meet the exclusion criteria; (2) Patients withdraw informed consent or refuse to participate in the research.

Pre-enrolled patients will receive three cycles of SOX. Then, tumor response evaluation will be carried out according to the Response Evaluation Criteria for Solid Tumors (RECIST) 1.1 [19]. Those who demonstrate stable disease (SD) or progressive disease (PD) will be excluded. Patients achieving complete response (CR) or partial response (PR) will be enrolled and assigned into either group A (six cycles of neoadjuvant chemotherapy with SOX) for another three cycles of SOX followed by D2 surgery or group B (three cycles of neoadjuvant chemotherapy with SOX) for D2 surgery. Figure 1 showed the study flow chart. The trial has been approved by the ethics committee of the Chinese PLA General Hospital, Beijing, China and registered prospectively in the World Health Organization International Clinical Trials Registry Platform (WHO ICTRP) with registration number ChiCTR1900023293 on May 21st, 2019. All patients are required to sign the written informed consent.

**Fig. 1 Fig1:**
[figure not shown]
Study Flow Chart

Primary endpoint: Pathological complete response rate (pCR%) based on Ryan’s 0–3 pathological tumor regression grade (TRG) system [20].

Secondary endpoints: R0 resection rate, three-year disease-free survival (3-y DFS), five-year overall survival (5-y OS) and safety.

The study started in October 2019. Local ethics committee approvals are expected in October 2020, the enrollment of the first patient in November 2020, the last patient completing the research in November 2027, database lock in June 2027 and publication in June 2028.

### Patient eligibility

#### Inclusion criteria

Non-bedridden, aged 18 to 70 years old;Eastern Cooperative Oncology Group (ECOG) score is 0 to 1;Histologically confirmed gastric adenocarcinoma;Have evaluable lesions based on RECIST 1.1;Stage III (cT3-4aN1-3 M0, American Joint Committee on Cancer (AJCC) TNM staging system 8th edition) gastric cancer confirmed by enhanced computer tomography (enhanced CT) and laparoscopic exploration (endoscopic ultrasonography (EUS) and magnetic resonance imaging (MRI) if necessary);The research center and the surgeon have the ability to complete standard D2 radical gastrectomy, and the gastrectomy can be tolerated by the patient;Laboratory test criteria: peripheral blood hemoglobin (Hb) ≥ 90 g/L, neutrophil absolute count ≥ 3× 10^9^ /L, platelet count (PLT) ≥ 100× 10^9^ /L, alanine aminotransferase (ALT) and aspartate aminotransferase (AST) ≤ 2.5 times the upper limit of normal (ULN), total bilirubin ≤ 1.5×ULN, serum creatinine (SCr) ≤ 1.5×ULN, and serum albumin (ALB) ≥ 30 g/L;Patients with heart disease, echocardiogram showing that the left ventricular ejection fraction ≥ 50%, electrocardiogram (ECG) is basically normal within 4 weeks before operation and with no obvious symptoms are acceptable;There is no serious underlying disease that could lead to an expected life expectancy < 5 years;Willing to sign the informed consent for participation and publication of results.

#### Exclusion criteria

Pregnant or lactating women;Positive pregnancy test for women in childbearing age. Menopausal women without menstruation for at least 12 months can be regarded as women with no possibility of getting pregnant;Refusal of birth control during the study;Prior chemotherapy, radiotherapy or immunotherapy;History of other malignant diseases in the last 5 years (except for cervical carcinoma in situ);History of uncontrolled central nervous system diseases, which could influence the compliance;History of severe liver diseases (Child-Pugh class C), renal diseases (endogenous creatinine clearance rate (Ccr) ≤ 50 ml/min or SCr > 1.5 ULN) or respiratory diseases; Uncontrolled diabetes and hypertension; Clinically severe heart disease, such as symptomatic coronary heart disease, New York Heart Association (NYHA) class II or more severe congestive heart failure, uncontrolled arrhythmia requiring drug intervention, or a history of myocardial infarction in the last 6 months;History of dysphagia, complete or partial gastrointestinal obstruction, active gastrointestinal bleeding and gastrointestinal perforation;On steroid treatment after organ transplant;With uncontrolled severe infections;Known dihydropyrimidine dehydrogenase deficiency (DPD);Anaphylaxis to any research drug ingredient;Known peripheral neuropathy (> NCI-CTC AE 1). Patients with only disappearance of deep tendon reflex need not to be excluded.

### Grouping

All eligible patients will be registered, pre-enrolled and receive three cycles of SOX. After tumor response evaluation using RECIST 1.1, patients achieving CR or PR will be enrolled [19]. Then randomization without stratification will be carried out by computer generated allocation using IBM SPSS Statistics 22, and enrolled patients will be randomly assigned (1:1) to Arm A or Arm B.

Arm A: Patients will be pre-enrolled and receive three cycles of SOX. After randomization, patients in Arm A will receive three more cycles of SOX (six cycles of neoadjuvant chemotherapy with SOX in total) followed by D2 gastrectomy. After which postoperative chemotherapy will not be recommended.

Arm B: Patients will be pre-enrolled and receive three cycles of SOX. After randomization, patients in Arm B will receive D2 gastrectomy (three cycles of neoadjuvant chemotherapy with SOX in total). After which postoperative chemotherapy using SOX will be recommended.

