### Sample size calculation

The primary endpoint of this trial is pCR rate. Based on the data from previous study, after three cycles of SOX, the PCR rate is about 7% (*p*_*0*_), and we estimated that with six cycles of SOX, the PCR rate can be increased to 15% (*p*). Based on the Z test, the null and alternative hypotheses are *H*_*0*_: *p*=*p*_*0*_; *H*_*1*_: *p*≠*p*_*0*_. With the statistical power of 0.8 (β=0.2), the type I error rate of 0.05 (α=0.05), when *Z* > marginal value, the *H*_*0*_ will be rejected and *H*_*1*_ will be accepted. Using the following formulas with the sampling ratio is 1:1 and the drop-out rate of 10%, the sample size is set at 262 per arm [23].
$$ n=p\left(1-p\right){\left(\frac{z_{1-\frac{\alpha }{2}}+{z}_{1-\beta }}{p-{p}_0}\right)}^2 $$Each participant center takes 400 to 1000 cases of gastric cancer per year and about 2% of patients can be enrolled. Thus recruitment can be completed in 2 years.

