### Statistical analysis

The pCR rate is defined as the rate of patients achieving pCR. The R0 resection rate is defined as the rate of R0 resection. The DFS is defined as the period from the time of surgery to recurrence or death. The OS is defined as the period from the time of surgery to death or last follow-up. Chi-square test will be used to compare patients’ characteristics, pCR rate and R0 resection rate between two arms. Survival curves will be estimated by the Kaplan-Meier method. Survival rate of DFS and OS will be compared respectively between two arms using a two-sided log-rank test. Both intention-to-treatment analysis (ITT, patients who receive any treatment after enrollment) and per-protocol analysis (PP, patients who receive all preoperative chemotherapy and surgery) will be performed. Missing data will be processed using multiple imputation. For loss of follow-up, ITT analysis and sensitivity analysis will be performed respectively.

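### The primary pCR test ignores response and stage data known before allocation; it is valid, but prespecified adjustment would be a nearly free gain in precision (minor)

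*Protocol article*

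**What the plan says.** Protocol article, Grouping: patients are first selected on response ("After tumor response evaluation using RECIST 1.1, patients achieving CR or PR will be enrolled"). On the method of allocation, the same section says that "randomization without stratification will be carried out by computer generated allocation using IBM SPSS Statistics 22". The allocation ratio is 1:1.

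Inclusion criteria: every patient must have a documented clinical stage, "Stage III (cT3-4aN1-3 M0, American Joint Committee on Cancer (AJCC) TNM staging system 8th edition"). Both T category (3 or 4a) and N category (1 to 3) can therefore vary among randomised patients.

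Sample size calculation: "The primary endpoint of this trial is pCR rate". The assumed rates are 7% after three cycles and 15% after six, with 80% power, two-sided alpha 0.05 and 262 per arm after 10% drop-out.

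Statistical analysis: the test for pCR is set in the sentence that opens "Chi-square test will be used to compare"; that sentence also covers baseline characteristics and R0 resection. DFS and OS are compared by log-rank test. No stratum, covariate or regression model is named.

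**The concern.** Randomisation comes after three cycles of the study regimen. At allocation the trial therefore already holds, for each patient, a measured response of that tumour to those drugs. The Discussion treats this response as showing whether the tumour is sensitive to SOX and makes it the gate to randomisation. The primary comparison then leaves it out, along with stage. CR/PR is measured before allocation, so it can properly be used as a baseline covariate.

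Two things are at stake. If CR/PR or stage predicts pCR, an unadjusted test is less precise than the data allow, in a trial sized for 80% power. In addition, the article plans to compare characteristics between arms but does not say what follows if they differ. A later adjustment prompted by an observed imbalance would be open to challenge; a prespecified one would not.

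This is not silence that an unseen analysis plan would fill, because the article states both the unstratified allocation and the test.

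**Working it through.** **1. The plan's own figure.** Inputs from Sample size calculation: 0.07 and 0.15, two-sided alpha 0.05, power 0.80, drop-out 10%.

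n = [0.07×0.93 + 0.15×0.85] × (1.960 + 0.842)² / 0.08² = 0.1926 × 7.849 / 0.0064 = 236.2 per arm; 236.2 / 0.9 = 262.4.

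This matches the stated 262. (The printed formula has one variance term and gives 157, or 175 after drop-out. That is a separate matter.) The check below uses 236 evaluable per arm (262 × 0.9 = 235.8).

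**2. Assumptions.** The article gives neither the prevalence of CR among responders nor the pCR rate by CR/PR, cT or cN. One binary pre-randomisation factor was therefore assumed, with prevalence q of 5, 10, 20 or 50% and odds ratio (OR) for pCR of 1, 2, 3, 5 or 10. Overall pCR was held at 15% and 7% by solving, in each arm, (1−q)·expit(b) + q·expit(b + ln OR) = overall rate.

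**3. Method.** 40,000 simulated trials per scenario, unstratified allocation, unadjusted chi-square against CMH on the factor. Type I error was taken with both arms at 11%. The share of outcome variance explained is R² = q(1−q)(r₁−r₀)² / [0.11×0.89], where r₁ and r₀ are the pCR rates with and without the factor. An adjusted analysis needs about 236(1−R²) per arm for the same precision.

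**4. Results** (ranges over the four prevalences).

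| OR | R² | Chi-square power | CMH power | Equivalent n per arm |
|---|---|---|---|---|
| 1 | 0 | 80.7-80.8% | 80.3-80.4% | 236 |
| 2 | 0.004-0.011 | 80.5-81.0% | 80.1-80.9% | 233-235 |
| 3 | 0.011-0.028 | 80.8-80.9% | 80.7-81.4% | 229-233 |
| 5 | 0.031-0.067 | 80.4-80.9% | 81.1-82.4% | 220-229 |
| 10 | 0.076-0.144 | 80.5-80.9% | 83.2-85.6% | 202-218 |

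The largest gain is 85.6 − 80.5 = 5.1 points (OR 10, q = 20%). At OR 1 or 2 CMH is between level and half a point lower.

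Analytic cross-check of the largest gain: the standard error is √(0.1926/236) = 0.0286, so the standardised effect is 0.08/0.0286 = 2.80. With R² = 0.144 it becomes 2.80/√0.856 = 3.03, and power is Φ(3.03 − 1.96) ≈ 0.857.

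**5. Validity.** Type I error under unstratified allocation is 4.9-5.3% for the chi-square and 4.7-5.1% for CMH.

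**6. Chance imbalance.** The 95th percentile of the between-arm difference in the factor is 4 to 9 percentage points. Multiplied by r₁−r₀, this moves the pCR difference by 0.6-0.9 points at OR 3 and 1.5-2.1 points at OR 10. The planned effect is 8 points and the standard error 2.9 points.

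**7. Would stratified allocation add anything?** Stratified allocation with CMH has power 79.8-85.8%, almost the same as adjustment alone. If allocation were stratified but the unadjusted chi-square kept, the test would become conservative: type I error is 3.6-4.4% at OR 10.

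**The case against.** The strongest reply is that nothing here is an error. Simple 1:1 randomisation followed by a chi-square test is a valid design and agrees with the two-proportion sample size. Chance imbalance is already part of the sampling error the test allows for. The article does not rule out a supporting adjusted analysis, and with about 524 patients large imbalances are unlikely. All of this stands, and it is why the point is minor.

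The size of the gain also rests on figures the article does not give. A reader might infer that CR at randomisation must be a very strong predictor. Assuming 5-15% CR, with pCR of 40-50% in CR and 6-9% in PR, the R² formula gives power of 83.2-86.6%, worth 46-104 extra patients. Those inputs imply odds ratios of about 8 to 13, and nothing in the article supports them; the Background gives only an overall response rate of 68.8% with no CR/PR split. Milder or rarer factors give much less by the same formula:

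- 10% CR, pCR 20% vs 10%: R² 0.009, power 80.3%.
- 10% CR, pCR 25% vs 9.5%: R² 0.022, power 80.8%.
- 2% CR, pCR 50% vs 10.2%: R² 0.032, power 81.2%.

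What survives is narrower. The primary test is fixed without covariates that are already in hand. Adjusting costs at most about half a point of power if they are weak and gains up to about 5 points if they are strong.

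**Conclusion.** The point holds as one of efficiency and robustness, at minor severity. With 236 evaluable per arm, adjustment for one pre-randomisation factor takes power from about 80-81% to about 80-86%. This assumes prevalence of 5-50% and an odds ratio of 1-10, with overall pCR rates of 7% and 15%. There is no useful gain at an odds ratio of 2 or below. No separate calculation was made for cT, cN, R0, DFS or OS.

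Two stronger readings are not supported. A reader might infer that the planned comparison is biased or its type I error inflated; it is not, since error stays near 5%. A reader might also infer that unstratified randomisation is itself a fault to be repaired; adjustment alone recovers nearly all the available gain.

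**What to change.** Before any outcome data are seen, prespecify a covariate-adjusted primary pCR analysis in one of two forms:

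- a CMH test stratified by RECIST response at randomisation (CR vs PR); or
- a logistic model with arm, CR/PR, cT (3 vs 4a) and cN (1, 2, 3), reporting the standardised risk difference with its 95% CI and test. This keeps the difference in pCR rates as the quantity estimated. The planned rates imply about 236 × (0.15 + 0.07) ≈ 52 pCRs, against five coefficients besides the intercept.

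Name CMH on CR/PR as the fallback if CR patients are too few for the model, and keep the unadjusted chi-square as a sensitivity analysis. Randomisation can stay as it is; if it is ever stratified, the analysis must include the strata.

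The cost is a few lines of text and a slightly more complex primary analysis. No new data, patients or visits are needed.
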